## Methods and analysis

### Study design and settings

This is a double-blind, sham-controlled pilot trial to examine the efficacy of rTMS on insomnia in ASD. Participants will be randomized to the rTMS group or sham rTMS group for 4 weeks (5 days/week). Assessments of the primary and secondary outcomes will be performed at baseline, after the 4-week treatment, and at the 4-week follow-up with rTMS or sham treatment (Figure 1). The protocol was approved by the Biomedical Research Ethics Committee West China Hospital of Sichuan University and is registered at the Chinese Clinical Trial Registry (ChiCTR2100049266).

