### Inclusion/exclusion criteria

Participants eligible for the trial must comply with all of the following:

1) A preliminary clinical diagnosis using DSM-5 in the Mental Health Center by a child psychiatrist will be confirmed by two well-trained child psychiatrists using the Autism Diagnostic Interview-Revised (ADI-R) and Autism Diagnostic Observational Schedule (ADOS-2) (35, 36).2) Age between 3 and 13 years.3) Patients with ASD must meet the following diagnostic criteria for insomnia in the International Classification of Sleep Disorders–Third Edition (ICSD-3) (duration > 3 months: difficulty sleeping (sleep latency > 20 min or wake-up time > 20 min after falling asleep) at least 3 nights per week, confirmed by sleep diary (at least 7 days) and portable home-PSG (2 consecutive nights, based mainly on the second-day monitoring data) (37).4) Not taking any drugs that affect sleep or no change in the drug dose and not taking new drugs during the trial period.5) Two living parents who are able to cooperate in signing the informed consent form and documents pertaining to related scales.

Participants will be excluded from the trial if they comply with one of the following:

1) Those who have a history of epilepsy or severe head trauma, who have medical device implants (such as pacemakers, etc.).2) Participants cannot cooperate.3) Severe neurologic or psychiatric disorders or medical conditions (e.g., skull defect and craniotomy) or other disorders likely to have an impact on sleep.

Participants who cannot tolerate the side effects (headache, etc.), develop any adverse events (seizure, etc.) during the treatment, or miss more than two rTMS treatment sessions in a row, or miss more than four sessions in total, will be withdrawn from this study.

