### Outcomes

The primary outcome of this study will be the difference in sleep onset latency between baseline and the end of treatment. Secondary outcomes will be differences in other parameters derived from polysomnography, the sleep diary, CSHQ, CARS, ABC, SRS, RBS-R, and metabolomics analysis.

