#### Safety outcomes

Family members will also be asked to complete an adverse event report every day, and this report will include information about potential side effects, including headache, nausea, vomiting, and seizures. If the above symptoms occur during treatment, treatment will be immediately stopped to see if these symptoms subside. If status epilepticus occurs, the patient will be sent to the emergency room for symptomatic treatment. Safety outcomes and treatment-related side effects will be assessed and reported in the publication.

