## Statistical analysis

We will use SPSS software version 26.0 (IBM Corp, Armonk, New York, US) to perform data analysis. Demographic and baseline data will be analyzed with standard descriptive statistics. Normally and non-normally distributed data will be presented as means (SDs) and medians (quartiles), respectively. The comparison of basic data between the rTMS group and sham rTMS group will be performed using Student's *t*-test, the chi-squared test, or the nonparametric test according to the data type. To verify the efficacy of our intervention, the final analysis will be conducted according to the intent-to-treat (ITT) principle, and missing data will be replaced by means of the last observation carried forward rules. Changes in quantitative variables over time (evaluation of the therapeutic effect of rTMS on variations in sleep latency) will be analyzed using random-effect models allowing us to take into account repeated measurements. Time (baseline, post, and 1-month follow-up) and group (rTMS or sham) effects will be estimated and tested, along the interaction with the group. According to the same strategy, changes in other quantitative variables over time will be investigated. To further analyze the relationship between the change in the parameter of sleep and clinical symptoms, logistic regression, general linear correlation or regression will be taken into consideration between various types of outcomes. The number and proportions of participants with side effects, adverse events, and serious adverse events will also be reported. All statistical analyses will be two-sided, and statistical significance will be set at p<0.05. For untargeted metabolomics analysis, principal component analysis (PCA) and partial least squares discriminant analysis (PLS-DA) will be performed in metaX (a flexible and comprehensive software for processing metabolomics data). We will apply univariate analysis (*t*-test) to calculate the statistical significance (*P* value). Metabolites with VIP > 1 and *P* value < 0.05 and fold change (FC)≥ 2 or FC ≤ 0.5 will be considered to be differential metabolites.

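### Children who must stop stimulation also leave the study; if primary sleep latency comes from PSG, carry-forward then scores their change as zero

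*Protocol article*

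**What the plan says.** All references are to the protocol article.

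- **Inclusion/exclusion criteria.** The triggers are alternatives. The first two are "Participants who cannot tolerate the side effects (headache, etc.), develop any adverse events (seizure, etc.) during the treatment". The third is to "miss more than two rTMS treatment sessions in a row". The fourth trigger and the shared consequence read "or miss more than four sessions in total, will be withdrawn from this study". All have the same consequence, and it concerns the study, not the stimulation. No section provides for assessment after withdrawal.
- **Study design and settings**, with Table 1: "Assessments of the primary and secondary outcomes will be performed at baseline, after the 4-week treatment, and at the 4-week follow-up". Home-PSG is ticked at those three times only.
- **Outcomes.** The primary outcome is the change in sleep onset latency from baseline to the end of treatment. Its source is not named, but the next sentence reads "Secondary outcomes will be differences in other parameters derived from polysomnography".
- **Statistical analysis.** On the analysis set: "the final analysis will be conducted according to the intent-to-treat (ITT) principle". On gaps in the data, the same sentence adds: "missing data will be replaced by means of the last observation carried forward rules". The same section plans random-effects models for the repeated measurements.

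**The concern.** Intention-to-treat needs an outcome for every randomised child, including those who stop treatment early. The withdrawal rule prevents that outcome from being collected, and carry-forward fills the gap with an assumption. Every trigger acts during the treatment weeks, before the post-treatment PSG. A child withdrawn then has a baseline PSG and nothing later, so the imputed change is baseline minus baseline.

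A child who stopped early but kept some benefit is therefore scored as having none, and so is a sham child who improved spontaneously. At stake is the primary estimate: it would partly reflect who was withdrawn, and the post-treatment data that could correct it would never have been collected.

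**Working it through.** **Inputs.** From Sample size: difference 10 min, SD 8.4 min, two-sided 0.05, power 80%, drop rate 10%, total 30. From Randomization and blinding: 1:1 allocation. From Study design: 5 sessions a week for 4 weeks, so 20 sessions. The withdrawal rates by arm, the improvement in the sham arm and the benefit kept after stopping are not in the document and are assumptions here. A two-sample t-test on change stands in for the random-effects model.

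**The plan's own figure.** By the noncentral t, 12 per arm gives 79.6% power and 13 per arm gives 82.9%. Then 13/0.90 = 14.4, rounded up to 15 per arm, or 30 in total. The stated sample size reproduces. Power is 88.2% at 15 per arm with no loss and 84.4% at 13.5 per arm, which is a plain 10% loss.

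**Reach of the missed-session clause.** A child who stops for good after session 17 misses sessions 18, 19 and 20. That is three in a row, which exceeds the limit of two. So any child who stops for good at session 17 or earlier is withdrawn, whatever the reason.

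**Effect of scoring zero.** Let pa and ps be the withdrawal fractions in the active and sham arms, and s the mean sham improvement.

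- Expected difference = (1 − pa)(10 + s) − (1 − ps)s
- Active variance = (1 − pa)8.4² + pa(1 − pa)(10 + s)²; sham variance has the same form with ps and s
- If pa = ps = p, the difference is 10(1 − p), whatever s is

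| pa | ps | s (min) | Difference (min) | Power at 15 per arm |
|---|---|---|---|---|
| 0 | 0 | any | 10 | 88.2% |
| 10% | 10% | 0 | 9.0 | 82.3% |
| 10% | 10% | 5 | 9.0 | 78.6% |
| 10% | 0 | 0 | 9.0 | 80.3% |
| 10% | 0 | 5 | 0.90 × 15 − 5 = 8.5 | 72.5% |
| 5% | 20% | 5 | 0.95 × 15 − 0.80 × 5 = 10.25 | not computed |

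For the second row, the active variance is 0.9 × 70.56 + 0.09 × 100 = 72.5 and the sham variance is 63.5, so the pooled SD is √68.0 = 8.25. The last row shows that the estimate can also be inflated.

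**Avoidable part.** If children who stop keep a fraction r of the benefit and are measured, the difference with no sham change is 10(1 − p) + 10pr. At p = 10% this is 9.0 min (r = 0), 9.5 min (r = 0.5) or 10 min (r = 1), against 9.0 min under carry-forward. The avoidable bias is thus 0 to 1 min. For scale, the standard error of the difference at 15 per arm is 8.4 × √(2/15) = 3.07 min.

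**Recruiting until 30 children complete (Trial status).** With 10% withdrawn in both arms, 15/0.90 = 16.7, so about 17 per arm are randomised and power is 87.0% (s = 0). The expected difference is still 9.0 min, because it does not depend on sample size.

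**The case against.** **The source of sleep latency is not stated.** The sleep diary also records time to fall asleep and is kept during treatment. If the diary were the source, an on-treatment value would be carried forward, not baseline. This stands, and the zero is conditional for that reason. PSG is the better reading: the Outcomes section calls the secondary PSG measures the other ones, and the Introduction stresses objective assessment. Under either reading, post-treatment data are lost by rule.

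**The effect is small.** At the midpoint the avoidable bias is 0.5 min, about one-sixth of a standard error, in a trial that calls itself a pilot. This also stands. If children who stop keep no benefit, measuring them does not change the expected estimate. But measuring them would show which case holds, while carry-forward assumes the answer.

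**Stronger readings that the document does not support:**

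- *About a quarter of children would be withdrawn.* A reader might infer this from the 25% in the Introduction. That figure is the rate of any adverse effect, described as mild and short-lived; it is not a withdrawal rate.
- *Any minor headache means withdrawal.* The eligibility wording gives headache as an example of a side effect, which leads to withdrawal only if not tolerated, and seizure as an example of an adverse event. Safety outcomes blurs the border somewhat, since "this report will include information about potential side effects, including headache, nausea, vomiting, and seizures", but it stops treatment to see whether symptoms settle. The point does not depend on this: the intolerance and missed-session clauses are enough.
- *The bias always works against rTMS.* It does with equal withdrawal, but not in general, as the 10.25 min example shows.

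**Withdrawal protects the child.** Stopping stimulation does that. Home-PSG and rating scales afterwards add no stimulation risk.

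**Conclusion.** The concern holds in conditional form. The stated rules remove children from the study for reasons that should only end stimulation. If the primary outcome is PSG sleep latency, carry-forward then assigns those children a change of zero. With equal withdrawal the difference shrinks in proportion, to 9.0 min at 10%, of which 0 to 1 min is avoidable. With unequal withdrawal and some sham improvement the direction is open.

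A reader might infer that the trial is left seriously underpowered. At 10% withdrawal that is not supported: with no sham improvement, power at 15 per arm is 80% to 82%, against 84% for a plain 10% loss, and recruiting to 30 completers raises it. It falls below 80% in the examples where sham children improve by 5 min, but that improvement is an assumption. The main harm is to the estimate. The results rest on the protocol's 10 min and 8.4 min, on assumed withdrawal rates, and on a t-test approximation. This is a cheap improvement worth making, not a fatal flaw.

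**What to change.** Two changes are needed, because either alone leaves part of the problem.

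1. **Inclusion/exclusion criteria, last paragraph.** Keep the triggers, but replace the consequence (withdrawal from the study) with: *will permanently discontinue stimulation but, in either arm and unless consent is withdrawn, will remain in the study and have the post-treatment and 4-week follow-up assessments on the scheduled dates.* No new rule on resuming sessions after a mild symptom is needed; that stays a clinical decision.
2. **Statistical analysis.** Drop last observation carried forward and fit the planned random-effects model to all observed data. Otherwise a child whose family declines the later assessments is still scored as unchanged.

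The cost is a short amendment, with no change to the sample size. Families of children who stopped stimulation are asked to complete home-PSG, scales and blood samples that are already scheduled, and some may decline. The trial is already recruiting, so data from children already withdrawn may not be recoverable.

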### Randomization and blinding

For participant allocation, a computer-generated random list will be used, which is based on the permutation block method with a random number generator and allocated at a ratio of 1: 1. A research assistant concealed the allocation sequence using sealed, opaque envelopes that contain the treatment information (A or B) before officially entering the study. After completing the consent form and baseline measures, the corresponding envelope for a given participant ID will be given to the rTMS therapist prior to the first rTMS session. The rTMS therapist is the only person who determines the treatment method (rTMS or sham treatment) for A or B. Once the treatment information is decided, no change will be accepted. Others, such as study investigators, parents, patients and statistical analysts, will be completely blinded to the treatment condition. Any adverse effects or body discomfort will be recorded after each rTMS treatment session. The aforementioned individuals will be unblinded to information about the treatment only when a participant experiences serious adverse events, and then an independent investigator will reveal the current treatment of this participant.

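### Read literally, one serious adverse event unblinds the statistical analysts, and because one fixed A/B code covers all children, it shows them every child's arm

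*Protocol article*

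**What the plan says.** All of this is in the protocol article, Randomization and blinding.

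- **Sequence.** A computer list with permuted blocks at 1:1 sets each child's letter. The block size is not given. A research assistant conceals the list in "sealed, opaque envelopes that contain the treatment information (A or B) before officially entering the study".
- **Handover.** Once consent and baseline measures are complete, "the corresponding envelope for a given participant ID will be given to the rTMS therapist prior to the first rTMS session".
- **Key.** "The rTMS therapist is the only person who determines the treatment method (rTMS or sham treatment) for A or B". The key is then fixed: "Once the treatment information is decided, no change will be accepted".
- **Blinded persons.** "Others, such as study investigators, parents, patients and statistical analysts, will be completely blinded to the treatment condition".
- **Exception.** "The aforementioned individuals will be unblinded to information about the treatment only when a participant experiences serious adverse events", at which point "an independent investigator will reveal the current treatment of this participant".

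The article does not say whether anyone besides the therapist sees the children's letters. Nor does it say how the independent investigator obtains the key.

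**The concern.** Breaking the code for one child in an emergency is normal practice. The difficulty is the combination of two choices. One key serves the whole trial, and the list of people told after a serious event includes some with no part in the child's care. Under a shared key, a fact about one child is also a fact about the key.

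What is at stake is mainly the analysts' blind. The Statistical analysis section leaves choices open: parametric or nonparametric comparison by data type, and logistic regression, correlation or linear regression for relating sleep change to symptom change. Blinding is what keeps such choices independent of the result. If outcome raters also had the letters, the clinician-rated CARS and the scoring of the home polysomnography would be exposed too.

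**Working it through.** The point is mostly one of logic, with two small calculations on its size.

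**1. Number of children.** The Sample size section gives a difference of 10 min, SD 8.4 min, two-sided 0.05, 80% power and 10% dropout. A two-sample t-test with standardised difference 10/8.4 = 1.19 needs 12.1 per arm, so 13 (power 79.6% with 12, 82.9% with 13). Allowing for dropout, 13/0.9 = 14.4, so 15 per arm and 30 in total. The stated 30 is reproduced and is used below only as a count.

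**2. Who is told.** The exception refers back to people already mentioned. The nearest such group is the list of blinded persons in "Others, such as study investigators, parents, patients and statistical analysts, will be completely blinded to the treatment condition". Taken literally, a serious event in one child therefore unblinds investigators, that family and the analysts.

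**3. What each learns.** The disclosed fact is one child's arm.

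- *Analyst.* To compare arms, the analyst must hold a two-group label for every child. If the affected child carries label A and is disclosed as active, then A is active and B is sham. The other 30 − 1 = 29 children are decoded. It makes no difference whether the labels arrive before or after the disclosure, provided the analyst can find that child's record.
- *Investigator or outcome rater with the letters.* The same result: 29 of 29.
- *Anyone without the letters.* Only inference within the permuted block remains. For block size b, the chance that another child in the same block is in the opposite arm is (b/2)/(b − 1). The block size is an assumption here:

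| Assumed block size | Same block | Other blocks |
|---|---|---|
| 2 | 1/1 = 1.00 | 0.50 |
| 4 | 2/3 = 0.67 | 0.50 |
| 6 | 3/5 = 0.60 | 0.50 |

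**4. How likely the trigger is.** The article gives no serious-event rate, so the per-child risk p is assumed. The chance of at least one event among 30 is 1 − (1 − p)^30:

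| Assumed p | Chance of at least one event |
|---|---|
| 0.5% | 14% |
| 1% | 26% |
| 2% | 45% |
| 5% | 79% |

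**5. Therapist and independent investigator.** One sentence makes the therapist the sole person who settles what the letters mean. Another has "an independent investigator will reveal the current treatment of this participant". For both to work, the independent investigator needs a copy of the key or a code-break for each child. Neither is mentioned.

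**The case against.** **The reveal is confined to the affected child.** This is true, and it protects the other children from anyone who lacks the letters. It does not protect the blind of someone who holds a group label for every child, as an analyst must.

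**Nothing says that investigators or raters see the letters.** This stands. The envelope goes to the therapist. A reader might infer that CARS ratings lose their blind across the whole trial after one event. The article does not support that without access to the letters.

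**The therapist does not control allocation.** This also stands. A reader might infer from "The rTMS therapist is the only person who determines the treatment method (rTMS or sham treatment) for A or B" that the therapist has discretion over who gets which treatment. But each child's letter comes from a concealed random list, and the key cannot change once set. Swapping the labels on a random 1:1 list leaves a random 1:1 list, so successive children cannot be steered to an arm. The wording may even mean only that the therapist is the one who knows the key.

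**The consequence is limited.** CARS is one of several secondary outcomes. The primary outcome is change in sleep onset latency, for which home polysomnography is the objective measure. The Introduction describes the adverse effects seen in children as mild and short-lived, and the probabilities above rest wholly on assumed risks. This bears on the size of the problem but does not remove it.

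**Code-break logistics belong in the full protocol.** This is fair as to where a key is stored, so it would go too far to say that emergency unblinding depends on reaching the therapist. The disclosure rule, however, is stated in the article and is not a matter of omitted detail. The sole-person wording and the independent investigator's role also still need to be reconciled.

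**Conclusion.** The point holds in a limited form. As written, the rule tells statistical analysts one child's treatment after a serious adverse event. With a single fixed key, that gives them the arm of all 30 children. This rests on three things: the literal reading of who is unblinded, an analyst who holds two-group labels, and an analyst who can identify the affected child's record. For investigators and outcome raters the trial-wide break is conditional on access to the letters. Families learn only their own child's arm, apart from what block structure lets them guess.

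How often the rule would be triggered cannot be derived from the article. No bias in the primary outcome has been shown, and no sample-size figure changes. The edit is still worth making, because the disclosure serves no purpose in the child's care and the trial's double-blind claim depends on this paragraph.

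**What to change.** 1. Reword the exception so that disclosure after a serious event goes only to those who need it for that child's safety. State that statistical analysts and outcome raters stay blinded until database lock. This is the essential change.
2. State that the A/B letters are withheld from investigators and outcome raters.
3. Use participant-specific codes for children still to be randomised, so that one disclosed code says nothing about another child.
4. Lodge a sealed code-break for each participant with the independent investigator, and reword the sentence on the therapist's sole role to match.

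Two other remedies would not work. New two-group labels for the analysts give no protection, because an analyst told one child's arm decodes any two-group label. Having the key sealed before the first allocation is no longer possible, because Trial status says recruitment began in July 2021.

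The cost is new envelope labels, a set of sealed code-breaks and a short protocol edit.
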